## Abstract

**Background:**

Nonadherence to medication is a major issue in patients with chronic disorders such as Parkinson’s disease (PD). Many interventions for increasing adherence have been tested, and these have shown weak-to-moderate efficiency. Although the best methods to improve adherence remain unclear, it is reasonable to use tailored interventions instead of the “one-size-fits-all” approach.

**Methods:**

A randomized, controlled, triple-blinded trial in elderly patients with PD is conducted to test the efficacy of AdhCare, a tailored intervention to enhance adherence compared with that achieved with routine care (64 participants per arm). Motor function, quality of life, and adherence measures will be assessed at baseline and at 3 and 6 months of follow-up. The type of intervention depends on the main personal reason for nonadherence (e.g., forgetting to take the medication or poor knowledge about the medication).

**Discussion:**

The results of this study will provide valuable information for health professionals and policymakers on the effectiveness of tailored interventions in elderly patients with PD.

**Trial registration:**

German Clinical Trials Register DRKS00023655. Registered on 24 February 2021. Last update on 22 March 2023.

## Administrative information

Note: the numbers in curly brackets in this protocol refer to SPIRIT checklist item numbers. The order of the items has been modified to group similar items (see http://www.equator-network.org/reporting-guidelines/spirit-2013-statement-defining-standard-protocol-items-for-clinical-trials/)

## Introduction

### Background and rationale {6a}

Poor adherence is a major issue in health care and is associated with increased morbidity, mortality, and immense costs for the health care system [1–4]. The treatment of chronic disorders usually includes the long-term use of pharmacotherapy and nonpharmacological therapy. However, their complete benefits are often not achieved because approximately 50% of patients either do not take medications as prescribed or do not follow recommendations (termed nonadherence) [5].

Because of demographic changes, the burden of neurological diseases in elderly patients in Germany is increasing, with a critical exacerbation of the problem of nonadherence, as the World Health Organization (WHO) quoted, “increasing the effectiveness of adherence interventions may have a far greater impact on the health of the population than any improvement in specific medical treatments” [6].

In the geriatric population, nonadherence contributes to adverse drug events, increased length of hospital stay and readmissions to hospitals, and lower quality of life [1, 2]. However, physicians often do not routinely enquire about patients’ adherence and are therefore unaware of the extent of patients’ nonadherence to medication.

Many factors contribute to nonadherence [7]. Nonadherence is a dynamic process and may be intentional (when the patient deliberately decides not to follow the recommended treatment) or unintentional (when the patient cannot follow the recommendation). Furthermore, nonadherence often occurs after discharge from the hospital [8–10]. Because the reasons for nonadherence are complex and diverse, interventions to improve adherence must be multifactorial and in the best case trans-sectoral. Although many interventions for increasing adherence have been tested, the best methods to improve adherence remain unclear [11]. Moreover, the available data are mostly restricted to internal medicine. However, it is reasonable to assume that effective intervention strategies must consider the distinct reasons for nonadherence (e.g., a patient who intentionally modifies their medication will not benefit from pill reminders) [12, 13].

More than 20% of adults aged ≥ 60 years experience a mental or neurological disorder (excluding headache disorders), and 6.6% of all disabilities (disability-adjusted life years) among adults aged ≥ 60 years are attributed to neurological and mental disorders [14]. Therefore, evidence-based data are urgently needed to improve adherence in neurogeriatric patients.

Based on the existing data from our large observational trial in the Department of Neurology of the University Hospital Jena, this project will develop a complex intervention to improve adherence in elderly patients with PD. The novel aspect of this intervention is to apply tailored interventions depending on the main personal reason for nonadherence. These personal reasons will be assessed using a detailed adherence self-report, named German Stendal Adherence with Medication Score (SAMS), and include modifications of medication without consulting the physician, forgetting to take the medication, and lack of knowledge about the prescribed medication [15–18]. The following questions will be addressed by the project:Can a specific intervention with either behavioral or educational strategy improve motor function and adherence?How are these interventions transduced and recognized by the various players in the health care system?

It has been shown that the choice of intervention depends on the feasibility and availability [13]. In this study, one of the key guiding principles is that the intervention is clinically practical and therefore implementable and can later easily be transferred into practice.

#### Objectives {7}

The objective of this study is to improve or maintain motor function by using a tailored intervention to improve adherence to medication in elderly patients with PD.

#### Trial design {8}

This study is based on the NeuGerAd study, a longitudinal observational study of adherence in older adults with neurological disorders [19]. The AdhCare trial is designed as a randomized, controlled, patient, observer, and data analyst-blinded superiority trial with two parallel groups and a primary endpoint of motoric function using UPDRS II and III. It is conducted to test the efficacy of AdhCare, a tailored intervention to enhance adherence compared with that achieved using routine care. The participants are assessed at baseline and at 3 and 6 months of follow-up.

A total of 130 participants are randomized in a 1:1 ratio: intervention in the AdhCare arm (*n* = 64) or control group with standard of care (*n* = 64).

## Methods: participants, interventions, and outcomes

### Study setting {9}

The study is conducted in the Department of Neurology at the University Hospital Jena, Germany.

Patients with PD presenting at our outpatient or inpatient movement disorder unit are included. All patients aged ≥ 60 years with PD are screened for eligibility and recruited after obtaining informed consent. Following our experience with similar studies in this cohort, the willingness of patients to participate in the study is high because there are no harmful interventions planned.

### Eligibility criteria {10}

The inclusion criteria are as follows: elderly patients (age > 60 years) with PD according to the Movement Disorder Society (MDS) criteria, self-management of medication, Montreal Cognitive Assessment (MoCA) ≥ 19, and nonadherence according to SAMS (SAMS ≥ 1).

The SAMS score serves as a basis for comparison and is an established questionnaire utilized to assess nonadherence. A threshold of ≥ 1 point is chosen to determine nonadherence. A score of 1 or higher is indicative of nonadherence, with the severity increasing as the score increases, leading to greater clinical significance.

The exclusion criteria are as follows: MoCA < 19, acute psychotic symptoms, delirium, no active involvement in drug management (e.g., bedridden in a nursing home), and inability to provide informed consent.

### Who will take informed consent? {26a}

The participants are screened by trained personnel and informed about the study by the subinvestigator if meeting the inclusion criteria. Informed consent is given in writing.

### Additional consent provisions for collection and use of participant data and biological specimens {26b}

N/a, as no biological specimens or data relating to this are collected.

### Interventions

#### Explanation for the choice of comparators {6b}

We chose a comparison and control arm to review the effect of the tailored intervention. Eligible Patients are randomized and either included in the control arm called AdhCare, where participants receive an additional tailored intervention according to their nonadherence pattern, or include in the comparison arm, where they do not receive any additional tailored intervention apart from the regular education sessions (standard of care).

#### Intervention description {11a}

Participants with any degree of nonadherence according to SAMS (SAMS ≥ 1) are randomized to the control arm or the AdhCare intervention arm. As it has been shown that implementation of fewer intervention strategies (in one patient) leads to better adherence outcomes [11], our approach is a tailored intervention that is adapted to the main reason for the individual patients’ nonadherence according to a self-reported adherence measure. Therefore, depending on the main reason for nonadherence according to SAMS (modifications, missing knowledge, and forgetfulness), the participants in the AdhCare arm receive a cognitive- or behavioral-focused intervention (Table 1).

**Table 1 Tab1:** Tailored intervention

Reason for nonadherence	Approach/focus	Particulars
1 Modifications	Educational/alternating strategies, e.g., adjusting the medication regimen	Addressing barriers Physician providing further treatment strongly involved
2 Missing knowledge	Informational/educational strategies to enhance knowledge, also about disease-related risks	Further sources of information are named
3 Forgetfulness	Behavioral: habit-based medication-taking reminders	Strong involvement of a life partner, if possible

The following interventions are provided to the AdhCare (intervention) group:

A standardized, informational talk to improve patient empowerment to take responsibility and control of their own health. Depending on the main reason for their nonadherence, we, among other things, perform the following interventions:Modifications: explain the medication, discuss barriers, and strive for patient empowerment to discover ways to improve the medication regimen and emphasize different ways of dealing with emerging problems other than cutting out on medications for instanceMissing knowledge: explain the medication and its indications, provide information about individual risks, and indicate other sources of informationForgetfulness: present and apply habit-based techniques to help the patient remember to take the medication and strive for patient empowerment to improve the medication regimenA written summary of the most significant aspects for their individual improvement of adherence.Their physician, who continue to provide treatment, are contacted and informed about the study, individual patients’ adherence problems and barriers, and possible strategies to minimize nonadherence in the particular patient.A follow-up telephone call to reinforce the respective focus about the medications and adherence after 2 weeks.

The control group received standard information about the course and therapy of PD.

#### Criteria for discontinuing or modifying allocated interventions {11b}

Whenever a participant expresses the desire to terminate the intervention or withdraws their consent, a discontinuation or modification of the assigned interventions is facilitated.

#### Strategies to improve adherence to interventions {11c}

Strategies to improve adherence to intervention protocols are not required because improving the adherence is the objective of the study and is measured in the participants. Patients are being called in advance by trained personnel to remind them of their appointments, so that the intervention and follow-ups could be carried out. Also, the collection of multiple questionnaires is facilitated by contacting patients by telephone and guiding them through the assessment.

#### Relevant concomitant care permitted or prohibited during the trial {11d}

There is no concomitant care/treatment allowed or prohibited during the study. We conscientiously inquire about and document the treatments that patients receive in order to be able to make statements regarding adherence (improvement) in this regard as well.

#### Provisions for post-trial care {30}

Arrangements for post-study care and compensation for individuals harmed by participation in the study are not necessary because of a cognitive- or behavioral-focused intervention.

### Outcomes {12}

#### Primary outcome

Because the overall goal is to improve patient-reported outcomes, the primary endpoint is motor function, which is assessed using the combined MDS revised Unified Parkinson’s Disease Rating Scale (MDS-UPDRS) II and MDS-UPDRS III after 6 months in the control versus AdhCare arm (intent-to-treat).

#### Secondary outcome

The secondary outcomes are as follows: self-reported adherence (SAMS), medication adherence scores, and number of primary care visits (Table 2). Moreover, we qualitatively evaluate the perception of intervention and barriers and facilitators for the implementation.

**Table 2 Tab2:** Study measures

	**Tool**	**Baseline**	**3 months**	**6 months**
Descriptive data: sociodemographic	Sex, age, education, income, employment, health insurance, housing	x		
Descriptive data: medical	Reason for admission to the hospital, inpatient or outpatient treatment, ICD-10 diagnoses, prescribed medication list, over-the-counter medication, medication actually taken, health service utilization			
Descriptive data: Parkinson motor	Hoehn and Yahr stage, MDS-UPDRS II, III, IV	x	x	x
Descriptive data: Parkinson nonmotor	MDS-UPDRS I, MoCA, PHQ-9, PDQ-8, GAI	x		x
Descriptive data: adherence	SAMS, change of medication within the 6-month period, difficulties in managing, handling, and swallowing pills	x		x
Descriptive data: comprehensive geriatric assessment	In addition to the aforementioned assessment tools, CIRS, IADL, visual acuity, hearing acuity, urinary incontinence, psychosocial circumstances, body mass index, hospital stay within the 6-month period	x		
Primary outcome: motor function	MDS-UPDRS II, III		x	x
Secondary outcome: self-reported adherence	SAMS			x
Secondary outcome: medication adherence scores	The proportion of self-reported number of pills taken among the number of pills prescribed by the doctor The proportion of the counted number of pills taken among the number of pills prescribed by the doctor		x	x
Secondary outcome: health care access	The number of primary care visits		x	x
Secondary outcome: adherence via medication subscription	The number and frequency of medication prescribed in the 6-month period and prescriptions redeemed at the pharmacy			x
Secondary outcome: qualitative	Perception of intervention and barriers and facilitators for the implementation			x

*ICD* International Statistical Classification of Diseases and Related Health Problems, *MDS-UPDRS* Movement Disorder Society revised Unified Parkinson’s Disease Rating Scale, *MoCA* Montreal Cognitive Assessment, *PHQ-9* Patient Health Questionnaire, *PDQ-8* Parkinson’s Disease Questionnaire, *GAI* Geriatric Anxiety Inventory, *SAMS* Stendal Adherence with Medication Score, *CIRS* Cumulative Illness Rating Scale, *IADL* Instrumental activities of daily living

#### Participant timeline {13}

At baseline and follow-up, the participants complete a staff-administered assessment and a self-report paper-based assessment. These assessments are summarized in Table 2. The time schedule is summarized in Table 3.

**Table 3 Tab3:** Time schedule

Time point	Study period			
	Enrollment, *-t*_*1*_	Allocation, 0	Post-allocation, *3 months*	Close-out, *6 months*
Enrollment				
Eligibility screen	X			
Informed consent	X			
Allocation		X		
Interventions				
*[AdhCare]*		X Cognitive- or behavioral-focused intervention		
*[Control]*		Standard information about the course and therapy		

#### Sample size {14}

We take as clinically relevant a difference of 5 points on the MDS-UPDRS II-III scale [20]. The group sample (control and comparison arm) sizes of 51 and 51 achieve 80.750% power to reject the null hypothesis of equal means when the population mean difference is 5.0 with a standard deviation for both groups of 8.8 and with a significance level (alpha) of 0.050 using a two-sided two-sample equal-variance *t*-test. The assumed values are based on the literature (see above [20]) and clinical experience. Considering 25% dropout, the final sample size is 64 participants per arm.

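### The 25% dropout allowance multiplies by 1.25 instead of dividing by 0.75, so 64 per arm leaves 48 evaluable patients, not the 51 that the stated power needs

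*Protocol article*

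**What the plan says.** Sample size {14} of the protocol article sizes the trial with a "two-sided two-sample equal-variance" t-test. It assumes that "the population mean difference is 5.0", "with a standard deviation for both groups of 8.8" and "with a significance level (alpha) of 0.050". On these inputs it reports that group "sizes of 51 and 51 achieve 80.750% power". It then sets the recruitment target: "Considering 25% dropout, the final sample size is 64 participants per arm".

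The abstract repeats "64 participants per arm". Trial design {8} also gives 64 in each arm, but opens with a different total: "A total of 130 participants are randomized in a 1:1 ratio", although 2 × 64 is 128. The article gives no other definition of the dropout rate and no other formula that leads to 64.

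**The concern.** A dropout rate is ordinarily the share of randomised patients who are lost. To finish with a required number, one divides that number by the share retained. Here the required number appears to have been increased by a quarter instead, which is a smaller allowance. If so, the trial falls short of its own target of 51 when dropout is exactly the 25% it plans for, and the quoted power does not belong to the quoted sample size.

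What is at stake is the accuracy of the design statement. Readers of the results, particularly of a null result, will use it to judge what difference the trial was able to detect.

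**Working it through.** **Inputs**, all from Sample size {14} unless noted: difference 5.0; SD 8.8 in both arms; two-sided alpha 0.05; 51 evaluable per arm; dropout 25%; 64 per arm. From Trial design {8}: total 130, ratio 1:1.

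**1. Reproduce the stated power.** For n per arm, the noncentrality is δ = 5/(8.8 × √(2/n)), and power comes from the noncentral t distribution with 2n − 2 degrees of freedom. At n = 51, δ = 2.87 and power is 81.1%. The plan states 80.75%. The 0.35-point gap is immaterial: an SD of about 8.84, which rounds to 8.8, gives 80.75%. The power figure therefore reproduces.

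**2. Reproduce the 64.**
- Multiplying: 51 × 1.25 = 63.75, rounded up to 64. This is the plan's figure.
- Dividing: 51/(1 − 0.25) = 68 per arm, or 136 in total.

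**3. Apply the plan's dropout rate to the plan's sample size.** 64 × 0.75 = 48 per arm, three short of 51. The dropout that 64 can absorb while keeping 51 is 1 − 51/64 = 20.3%.

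**4. Power and detectable difference by the sizing t-test.**

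| Evaluable per arm | How it arises | Power for 5 points | Difference detectable with 80% power |
|---|---|---|---|
| 51 | the plan's requirement; 68 × 0.75 | 81.1% (stated 80.75%) | 4.93 |
| 48 | 64 × 0.75 | 78.7% | 5.08 |
| 48.75 | 65 × 0.75, from the total of 130 | about 79.3% | 5.04 |

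The loss at 48 is 80.75 − 78.7 ≈ 2.1 points against the stated figure and 81.1 − 78.7 = 2.4 points against the recomputed one.

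**5. Does the total of 130 rescue the figure?** No. It means 65 per arm, which tolerates 1 − 51/65 = 21.5% dropout. Even 49 evaluable per arm gives 79.5%.

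**6. What baseline adjustment could do.** The article gives no baseline-to-6-month correlation r, so this step is an assumption shown over a range. If 8.8 is the SD of the raw 6-month score, adjustment reduces it to 8.8 × √(1 − r²). At 48 per arm:

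| Assumed r | Residual SD | Power |
|---|---|---|
| 0.2 | 8.62 | 80.3% |
| 0.3 | 8.39 | 82.3% |
| 0.5 | 7.62 | 88.9% |
| 0.7 | 6.28 | 97.1% |

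If 8.8 is already the SD of a change score or of an adjusted residual, applying this factor would count the gain twice, and the table does not apply. The article does not say which SD it is.

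**The case against.** The strongest objection is that 78.7% is the power of an unadjusted t-test on completers, which is not the planned primary analysis. The Statistical methods section {20a} specifies a linear mixed model with the baseline value as a covariate, using all available follow-up from everyone randomised. Motor function is also measured at 3 months, so a patient lost after that visit still contributes. A reader might infer from the shortfall that the trial's true power is below 80%. The documents do not support that: the figure holds only for the sizing t-test, and under one reading of the SD a correlation of about 0.2 already brings power back to 80%.

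A reader might equally infer that the adjusted analysis certainly makes up the loss. The documents do not support that either, since they give no correlation and do not identify the SD.

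Two further objections concern weight. The effect is three evaluable patients per arm and about two power points, probably less than the uncertainty in inputs taken from literature and clinical experience. And with recruitment ended on 03 March 2023, no estimate, test or alpha level changes. Both are fair and limit the importance of the point. Neither makes the sentence correct, because the article rests its justification on the t-test and on 51 per arm, and 64 × 0.75 is not 51. Nor is this a detail left to a fuller document: the inputs, the rate and the result are all stated, and they disagree.

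**Conclusion.** The point stands as an arithmetic error of small size. An allowance for 25% dropout on 51 per arm is 68, not 64. The stated 64 covers about 20% dropout. At the planned 25%, the sizing t-test has 78.7% power for 5 points, and its detectable difference moves from just below to just above the 5 points that the trial calls clinically relevant.

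This rests on reading dropout as a share of those randomised, on the article's own difference, SD and alpha, and on a completer t-test as the sizing method. It makes no claim about the power of the planned mixed model, in either direction. The mismatch between a total of 130 and two arms of 64 is a separate inconsistency and adds no weight here.

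**What to change.** Do not enrol more patients. Reword the last sentence of Sample size {14} in one of two ways:

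- *64 participants per arm allow for about 20% dropout*; or
- *with 25% dropout, 48 participants per arm remain, giving about 79% power for a 5-point difference by t-test*.

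Optionally, add that the baseline-adjusted mixed model may recover the loss. If so, state which SD the 8.8 is, and give the gain as an assumption with a range: about 80%, 82%, 89% and 97% power at 48 per arm for correlations of 0.2, 0.3, 0.5 and 0.7, only if 8.8 is the SD of the raw 6-month score. Carry the same wording into the results paper.

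The cost is one corrected sentence and a slightly less favourable design statement. The analysis is unaffected.

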#### Recruitment {15}

To maximize participant enrollment, several strategies are being employed, including screening of both inpatients and outpatients of our movement disorder unit in the Department of Neurology at the University Hospital Jena, Germany, to capture a wider range of participants with varying medical conditions, severity levels, and treatment settings. Also, the first patient information is taking place through the attending physicians of our movement disorder unit. During this first contact, the advantages that the study brings to the participants are highlighted.

